### Outcome measures

The primary outcome measure will be the change in PTA (dB) from the first audiogram to the 30-day follow-up audiogram. Hearing will be evaluated using air-conducted and bone-conducted PTA after 1 and 14 days of treatment, and at 30 and 90 days of follow up.

Secondary outcome measures will include PTA at 90 days, visual analog tinnitus scale, visual analog vertigo scale, visual analog aural fullness scale, fasting blood glucose and 2-h postprandial blood glucose during treatment, and the change in glycosylated hemoglobin (HbA1C) levels. Vital signs and otological physical examination will be performed at each follow-up visit (Fig. 2).

**Fig. 2 Fig2:**
[figure not shown]
Schedule of study events. HbA1C, glycosylated hemoglobin

### Safety assessments

Study participants will be requested to report all adverse events (AEs) at each follow-up visit. All AE reports will be recorded and assessed by the investigators. Blood test, urinalysis, hemagglutination test, and electrocardiograph examinations will be performed before and after the treatment. All abnormal changes from baseline laboratory test results will be evaluated. Other safety test parameters will be measured at the discretion of the treating physician and will be based on the patient’s medical history.

### Sample size calculation

The purpose of the proposed study is to compare the effectiveness of PTA by one-sided *t* test, which is used with the 95% confidence interval method. The difference in PTA is reported in previous publications as 30.7 in the experimental group and as 28.7 in the control group. The difference in the mean was 2, and the combined standard deviation was 3. The type 1 error was 2.5% and statistical power was 90%. Considering a 5% loss rate, 96 samples are required. This allows for 48 participants in the study group and 48 in the control group.

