**Methods/design:**

The proposed study is a prospective, randomized superiority trial. A total of 96 patients (48 in each group) will be randomized into the experimental or control group. Patients in the experimental group will receive four 1-mL doses of 40 mg/mL of methylprednisolone over a 1-week period, with a dose administered every 2 days via tympanic membrane injection into the middle ear. The control group will be administered intravenous methylprednisolone (1 mg/kg/day, maximal dose 60 mg/day) for 5 days. The primary outcome for this study is the change in hearing threshold from the first audiogram to the 30-day follow-up audiogram. Secondary outcome measures will include pure-tone average (PTA) at 90-day follow up, visual analog tinnitus scale, visual analog vertigo scale, visual analog aural fullness scale, fasting blood glucose and 2-h postprandial blood glucose during treatment, and the change in glycosylated hemoglobin (HbA1C) levels. Vital signs and otological physical examination will be performed at each follow-up visit.

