## Background

Sudden sensorineural hearing loss (SSNHL) is usually defined as a sensory neural hearing loss greater than 30 dB across three contiguous pure-tone frequencies occurring within 72 h [1]. The annual incidence of SSNHL is 27 per 100,000 in the USA [2]. Diabetes mellitus is a risk factor as well as a poor prognostic factor for SSNHL [3]. The incidence of SSNHL is 1.54-fold higher in patients who have diabetes mellitus compared to patients who do not [4]. Although the standard treatment for SSNHL is systemic corticosteroid administration, this treatment results in loss of glycemic control in patients with diabetes mellitus.

Long-term hyperglycemia in patients with diabetes mellitus may lead to microangiopathy of the inner ear, which results in sensorineural hearing loss [5]. Previous animal and human studies have demonstrated that hair cell loss is observed in the temporal bone as well as thickened and damaged capillary walls of the stria vascular in animals and humans with diabetes mellitus [6]. Several studies have demonstrated that systemic corticosteroid administration in patients with diabetes mellitus and SSNHL had no advantage in hearing improvement when compared to other treatments [7–10]. Moreover, the use of systemic corticosteroids may result in side effects such as insomnia, weight gain, gastritis, mood changes, photosensitivity, and hyperglycemia [1]. Hyperglycemia may further affect the prognosis in SSNHL and patients with diabetes mellitus may be required to increase their insulin intake [9].

An alternative treatment strategy for SSNHL is intratympanic corticosteroid administration via direct injection into the middle ear [1]. Intratympanic treatment may increase drug concentration to the target organ. Parnes et. al. demonstrated higher inner ear corticosteroids levels after intratympanic corticosteroid administration compared to systemic administration in animal models [11]. A multi-center, randomized controlled trial in 250 patients involved comparison of intratympanic versus systemic corticosteroid therapy for SSNHL: the improvements in hearing outcomes were equivalent [12]. The benefit of intratympanic compared to oral treatment is reduced systemic steroid exposure and associated systemic adverse effects [1, 12]. A non-prospective randomized controlled trial that compared systemic versus intratympanic corticosteroid treatment showed improved hearing outcomes in patients with diabetes mellitus and SSNHL.

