Intratympanic corticosteroid treatment is an alternative primary treatment option for patients with diabetes mellitus and SSNHL. Intratympanic administration of corticosteroids provides a direct route into the inner ear via the round window membrane, while systemic corticosteroids have a limited ability to reach the inner ear due to the blood–labyrinthine barrier [21]. Intratympanic corticosteroid administration has been shown to achieve higher concentration levels in the inner ear compared to systemic administration, in both animal and human studies [11, 22]. Several studies have shown that intratympanic corticosteroid administration is as effective as systemic corticosteroids for hearing improvement [12, 23, 24]. In 2011, Rauch et al. [12] performed a multicenter, prospective randomized controlled trial comparing the outcomes of primary treatment with oral prednisone and intratympanic methylprednisolone administration. They observed a mean PTA improvement of 30.7 dB in the oral prednisone group compared to 28.7 dB improvement in the intratympanic group. They dismissed the idea that intratympanic administration was inferior to that of oral administration.

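### The sample size credits the intratympanic arm with a 2 dB advantage that the article's own Discussion reports the other way round, so the cited evidence does not support the sign of the planning effect

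*Protocol article*

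**What the plan says.** The Sample size calculation section of the protocol article takes its planning effect from the literature: "The difference in PTA is reported in previous publications as 30.7 in the experimental group and as 28.7 in the control group". It continues: "The difference in the mean was 2, and the combined standard deviation was 3". The error rates follow: "The type 1 error was 2.5% and statistical power was 90" per cent. The result is 96 patients, 48 per arm, said to allow for 5% loss. No reference number is attached to the two means, and the SD has no source.

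The abstract fixes which arm is which. For the new treatment, given by injection through the tympanic membrane: "Patients in the experimental group will receive four 1-mL doses of 40 mg/mL of methylprednisolone over a 1-week period". For the comparator: "The control group will be administered intravenous methylprednisolone".

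The Discussion reports the multicentre randomized trial of oral prednisone against intratympanic methylprednisolone (reference 12): "They observed a mean PTA improvement of 30.7 dB in the oral prednisone group compared to 28.7 dB improvement in the intratympanic group". It adds that this trial rejected inferiority of the intratympanic route. The Background says of a 250-patient randomized trial with the same reference number that "the improvements in hearing outcomes were equivalent".

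The Statistical analysis section sets a one-sided test of intratympanic superiority and cites reference 12 for its definition of superiority.

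**The concern.** The same two figures appear in two places with the arms exchanged. In the sample size section the larger improvement belongs to the intratympanic arm. In the Discussion it belongs to the systemic arm. Both cannot be right.

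The sign matters because the primary test is one-sided. A 2 dB difference in favour of intratympanic treatment and a 2 dB difference against it lead to the same patient number but to opposite expectations for the trial. The 2 dB is also presented as a published finding rather than as a target chosen by the investigators. A reader would conclude that a randomized trial had already observed the advantage on which 90% power is claimed. By the article's own account, it had not.

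**Working it through.** **Same source?** The sample size section refers only to earlier publications. The pair 30.7 and 28.7 occurs in one other place, the Discussion's account of reference 12. No other study with these means is offered.

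**The two sections side by side**

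| | Intratympanic (experimental) | Systemic (control) | Intratympanic minus systemic |
|---|---|---|---|
| Sample size calculation | 30.7 dB | 28.7 dB | +2.0 dB |
| Discussion | 28.7 dB | 30.7 dB | −2.0 dB |

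**Reproducing the plan's figure.** Inputs from the sample size section: difference 2, SD 3, one-sided α 0.025, power 0.90.

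n per arm = 2 × (1.960 + 1.282)² × 3² / 2² = 47.3, rounded up to 48, so 96 in total. The t-based calculation gives 49 per arm, 98 in total.

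The difference enters squared, so exchanging the arms leaves 96 unchanged. The 96 is, however, the number before loss: 48 / 0.95 = 50.5, or 51 per arm and 102 in total. That is a separate defect, but it affects the power to be restated.

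**Power with the sign kept.** With d = intratympanic minus systemic improvement:

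P(superiority shown) = Φ(d / SE − 1.960), where SE = SD × √(2/n).

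At SD 3 and n = 48, SE = 3 × √(2/48) = 0.612.

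- d = +2: Φ(3.266 − 1.960) = 90.4% (noncentral t 89.8%).
- d = +2 after 5% loss (45.6 per arm, SE 0.628): 88.9% (noncentral t 88.3%).
- d = 0: Φ(−1.960) = 2.5%, whatever the SD.
- d = −2: Φ(−3.266 − 1.960) ≈ 9 × 10⁻⁸ (noncentral t 1.0 × 10⁻⁷).

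**Dependence on the SD.** Because the SD of 3 is unsourced, d = −2 was repeated at 48 per arm over an assumed range. Only the value 3 stands in the article.

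| SD (dB) | P(superiority shown) at d = −2 |
|---|---|
| 3 | about 1 × 10⁻⁷ |
| 5 | 0.004% |
| 10 | 0.16% |
| 15 | 0.45% |
| 20 | 0.71% |
| 25 | 0.93% |

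The value moves by several orders of magnitude but stays below 1% throughout.

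**Direction of the decision rule.** The Statistical analysis section calls intratympanic treatment superior when the systemic group's mean change is the larger one. It describes the change as a difference between baseline and day 30 without giving the order.

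- As improvement (baseline minus day 30), the Discussion's result is 30.7 systemic against 28.7 intratympanic. The rule would count that as intratympanic superiority.
- As day 30 minus baseline, it is −30.7 against −28.7. The systemic value is then the smaller, and the rule would not be met.

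The calculations above assume the test runs in the direction of the stated hypothesis, greater improvement with intratympanic treatment. The article does not fix the sign that would guarantee this.

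**The case against.** The strongest reply is that the trial is not shown to be hopeless. A reader might infer from the −2 dB figure that it has essentially no power and cannot succeed. The article does not support that. The cited trial used an oral comparator, and nothing in the article describes its patients as diabetic. The present trial uses an intravenous comparator in diabetic patients. The Background and Discussion treat the earlier result as equivalence, not as harm from the intratympanic route. The near-zero probability applies only if −2 dB is the true effect here, and 10⁻⁷ applies only at the unsourced SD of 3. This objection stands, and the figures must be read as conditional.

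A reader might also infer that no evidence in the article favours intratympanic treatment. That goes too far as well: the Discussion describes a pilot with 40 dB improvement in 7 intratympanic patients against 30 dB with systemic treatment. The pilot is not, however, the stated basis of the calculation. The article says that it supported the calculation, which presents it as corroboration. It comes without an SD or a systemic-arm count, and its 10 dB difference is not the 2 dB used.

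Third, the power is not miscalculated for the alternative stated, since 48 per arm does give about 90% at +2 dB and SD 3. That is true. The fault lies in where the alternative is said to come from.

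Last, the source is not available, so the Discussion cannot simply be taken as the correct version. Its remark that inferiority of the intratympanic route was rejected fits the lower figure belonging to that route, but this is not proof.

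**Conclusion.** The concern holds in a limited form. The article contradicts itself on which route had the larger improvement. On its own fuller account of the cited trial, the +2 dB planning effect has the wrong sign. The claim that earlier publications reported a 2 dB intratympanic advantage is therefore unsupported by the only source shown.

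The number 96 does not change because of the swap. Power is about 90% for a true +2 dB with SD 3 at 48 per arm, and about 88–89% after 5% loss. The chance of showing superiority is 2.5% at no difference, and below 1% at −2 dB for SDs from 3 to 25. These figures assume normal outcomes with a common SD, SDs above 3 that are not in the article, and a test directed at greater intratympanic improvement. They do not establish what the true effect is in this population.

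This should be corrected before the sample size paragraph is relied on, because it is the stated justification for the size of a one-sided superiority trial.

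**What to change.** 1. Check the two means against the cited publication, and make the Sample size calculation and Discussion sections agree.
2. Remove the statement that a 2 dB intratympanic advantage was reported in earlier publications.
3. State the target difference as an explicit assumption with its rationale, and give a source or reason for the SD. If the pilot is part of the rationale, say so and report its SD and both arm sizes.
4. Restate the power, or the detectable difference, of 96 patients after 5% loss. By the normal approximation, the difference detectable with 90% power at 45.6 per arm is (1.960 + 1.282) × SD × √(2/45.6) ≈ 0.68 × SD, which is 2.04 dB at SD 3.
5. In the same edit, define the sign of the change in PTA, for example as baseline minus day 30 so that positive values mean improvement. Word the superiority rule in the Statistical analysis section to match. Correcting the arm labels alone would leave the direction of the test open.

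The cost of the correction is rewording, and the stated justification and power become less favourable. Whether 96 patients remain enough depends on the target and SD then chosen; with the present inputs and 5% loss the formula already asks for about 102.

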## Method/design

### Design and setting

This study will be a randomized controlled trial that will be performed at the Peking University Shenzhen Hospital in China. We will enroll 86 patients with diabetes mellitus and SSNHL over a 3-year period. Study participants will be randomized at a ratio of 1:1 to receive either intratympanic methylprednisolone or intravenous methylprednisolone (Fig. 1). The study protocol will follow the Standard protocol items: recommendation for interventional trials (SPIRIT) recommendations for interventional trials (Additional file 1).

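### The 96 patients leave out the stated 5% loss: 48 per arm is the number needed with complete data, so power after that loss is about 88%, not 90%

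*Protocol article*

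**What the plan says.** The Sample size calculation section of the protocol article gives every input needed to check its result.

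- Test: "The purpose of the proposed study is to compare the effectiveness of PTA by one-sided" *t* test.
- Error rates: "The type 1 error was 2.5% and statistical power was 90" per cent.
- Effect and spread: "The difference in the mean was 2, and the combined standard deviation was 3".
- Result: "Considering a 5% loss rate, 96 samples are required".
- Split: "This allows for 48 participants in the study group and 48 in the control group".

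The Design and setting section fixes equal allocation: "Study participants will be randomized at a ratio of 1:1". The Abstract repeats 96 patients, 48 in each group. The Statistical analysis section confirms the one-sided *t* test on the change in PTA from baseline to day 30.

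**The concern.** The article presents 96 as the total after allowing for 5% loss. If that were so, the same inputs with no loss would give a smaller number, about 91. They give 96. A reader would therefore believe that the trial can lose 5% of its patients and still have 90% power, when nothing has been set aside for loss.

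Loss is a practical matter here. The primary outcome needs an audiogram at day 30, follow-up runs to day 90, and the Data management and quality control section lets patients withdraw at any time for any reason.

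**Working it through.** **Inputs.** All come from Sample size calculation, except the allocation ratio, which is in Design and setting.

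- Difference δ = 30.7 − 28.7 = 2 dB
- Standard deviation σ = 3 dB
- One-sided α = 0.025, so z = 1.960
- Power 90%, so z = 1.2816
- Allocation 1:1
- Loss 5%

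**Step 1: reproduce the stated figure.** The normal formula per arm is

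n = 2(z₁₋α + z₁₋β)² σ²/δ² = 2 × (1.960 + 1.2816)² × 9/4 = 47.28.

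Rounded up, this is 48 per arm and 96 in total. It matches the article exactly, with no loss included.

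**Step 2: use the test the plan names.** With the noncentral *t* distribution, power is 89.8% at 48 per arm and 90.4% at 49. The *t* test therefore needs 49 per arm (98 in total) before any loss.

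**Step 3: apply the 5% loss in each standard way.**

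| Starting n per arm | Calculation | Per arm | Total |
|---|---|---|---|
| 47.28 (unrounded) | 47.28 / 0.95 = 49.77 | 50 | 100 |
| 47.28 (unrounded) | 47.28 × 1.05 = 49.65 | 50 | 100 |
| 48 (normal, rounded) | 48 / 0.95 = 50.5 | 51 | 102 |
| 49 (*t* test) | 49 / 0.95 = 51.6 | 52 | 104 |

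None gives 96. The shortfall is 4 to 8 patients in total, or 6 to 8 if n is rounded up before it is inflated.

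**Step 4: try other readings of α.** With one-sided 5%, n = 38.54 and 38.54 / 0.95 = 40.6, about 41 per arm. With two-sided 2.5%, n = 55.85 and 55.85 / 0.95 = 58.8, about 59 per arm. Neither explains 48.

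**Step 5: power if 96 are randomised and 5% are lost.** The evaluable number is 96 × 0.95 = 91.2, or 45.6 per arm.

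- Normal approximation: δ / (σ√(2/n)) = 2 / (3 × √(2/45.6)) = 3.183. Then 3.183 − 1.960 = 1.223, and power is 88.9%.
- *t* test: 88.3% at 45.6 per arm, and 88.2% with 46 and 45 analysed.

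For comparison, with complete data on 96 patients power is 90.4% by the normal approximation and 89.8% by the *t* test.

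**The case against.** The arithmetic itself is not in dispute. The case on the other side is about size and presentation.

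- **Two methods are in play.** The figure of 48 with no loss comes from the normal approximation, and the 88% comes from the *t* test. Within either method alone, the loss costs about 1.5 points: 90.4% to 88.9%, or 89.8% to 88.3%. Part of the gap from 90% is thus a matter of method. This stands, but either method used throughout leaves power below 90% after loss.
- **102 is not the only correct total.** Inflating the unrounded figure gives 100. This also stands, and it is why the shortfall is given here as 4 to 8.
- **The SD is printed as a whole number.** If it had been 2.94, the formula would give 2 × (1.960 + 1.2816)² × 2.94²/4 = 45.41, and 45.41 / 0.95 = 47.80, or 48 per arm with the loss included. The article does not state such a value, and 48 is exactly the no-loss figure for an SD of 3. Omission of the allowance is the likelier explanation.
- **Other problems in the planning are larger.** Sample size calculation assigns the 30.7 dB improvement to the experimental arm, while the Discussion assigns it to the oral prednisone arm of the cited trial. Design and setting gives an enrolment of 86, not 96. At 43 per arm with no loss, power is 86.3% by the *t* test. These points deserve their own correction, but they do not make the sentence about the loss rate true.

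**Conclusion.** The concern holds. On the article's own inputs, 96 is the total for complete data, and the claim that it already covers a 5% loss is wrong. Including the loss takes 100 to 104 patients. With 96 randomised and 5% lost, power is 88.3% by the planned *t* test, or 88.9% by the normal approximation.

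The effect on power is minor: one to two points below the stated 90%, with no change to the analysis or the decision rule. It is worth correcting because the section makes a complete numerical claim that its own figures contradict.

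The conclusion rests on two conditions. Patients who are lost are taken not to contribute to the day-30 comparison, which is what a loss allowance means. The difference of 2 dB and the SD of 3 dB are taken as printed. This check tests the arithmetic and does not endorse those inputs.

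**What to change.** Replace the sentence on the loss rate in Sample size calculation with, for example: *Under these assumptions, 48 patients per arm give about 90% power with complete data. With 5% loss (about 91 evaluable patients), power is about 88%.* This costs one sentence and about two points of stated power. Recruitment is unchanged.

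If the sponsor prefers to keep 90% power after loss, give 102 (51 per arm) as the total that includes the allowance. With 5% loss this leaves 51 × 0.95 = 48.45 per arm, between the *t*-test powers of 89.8% at 48 and 90.4% at 49. Rounding up throughout by the *t* test gives 104. The cost is 6 to 8 more patients, and the Abstract must then carry the same number.

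In either case, name the method used (normal approximation or *t* test), and bring the enrolment of 86 in Design and setting into line with the total that is kept.

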### Data management and quality control

Data collected in this trial will be derived from case reports. The collected data will be entered using the double-entry method at the end of every patient visit.

To ensure a high standard of outcome assessment in accordance with the trial protocol, physicians, assessors, and research assistants will attend a 5-h training workshop before the commencement of the trial. They will also be provided with a written protocol and standard operation procedures. All data gathered from different sites will be verified regularly by a researcher from the Peking University Shenzhen Hospital and will be overseen by study monitors. The monitoring tasks for the trial will be entrusted to the Clinical Research Center of Guangzhou University of Chinese Medicine (Guangzhou, China).

Study participants may withdraw from the study for any reason at any time. If a patient wishes to quit the study, the clinician will ask if they are willing to complete the evaluation based on the research schedule and record the last period during which they took their medication. The incidence of loss to follow up or withdrawal of participants will be recorded and reported.

